### Usual care (control group)

The physicians will treat the patients assigned to the usual care group based on their own, unrestricted criteria, using any resources available that they may consider appropriate.

### Procedure for identifying and recruiting patients

The following procedure will be used to select and recruit the patients:Using the list of active diagnoses in the computerised clinical records, a search will be performed for cases among the rosters of the participating physicians. The search codes and diagnoses (ICD-10; International Classification of Diseases, 10^th^ Edition) will be: M15 (polyarthrosis), M16 (coxarthrosis), M17 (gonarthrosis), M19 (other arthrosis), M47 (spondylosis), M50-M51 (disc disorders), M54.2 (cervicalgia), M54.3 to M54.5 (lumbago), M54.6 to M54.9 (dorsalgia), M25.5 (joint pain), M79.6 (limb pain), R52.1-R52.2 (chronic pain).Patients identified using these diagnoses will have their clinical history reviewed manually. Based upon the information available, patients will be ruled out if it is established that they do not meet inclusion criteria.The remaining individuals will be sent a letter with general information about the study and an invitation to participate. They will be notified of an upcoming telephone contact to verify their eligibility.Two weeks later they will receive a telephone call during which, with the patient’s consent, screening tests will be administered in order to identify the individuals with moderate to severe pain (BPI) for at least 3 months, as well a positive screening for major depression (PHQ-9).Patients positively screened for chronic pain and depression will be selected for an in-person interview with an independent interviewer to confirm whether they meet the inclusion/exclusion criteria and to obtain their informed consent in writing.

### Measurements

Standardised self-report scales will be given in person (during baseline interview) and on the telephone (follow-up interviews at 3, 6, and 12 months after recruitment). Questionnaires will be administered by an independent qualified interviewer. The interviewer will be blind to participant’s group.

### Measurement variables and tools (Table 1)

**Table 1 Tab1:** Study variables

Instrument	Assessment area	Time (s) of assessment
Brief Pain Inventory (BPI). Average pain scale	Pain severity	Screening
Patient Health Questionnaire (PHQ-9)	Depression symptoms	Screening
Sociodemographic data form	Age, sex, marital status, educational level, labour status, social class	Baseline
SCID (DSM-IV). Major depression module	Major depression diagnoses	Baseline
Duke Severity of Illness Checklist (DUSOI)	Medical comorbidity	Baseline
PRIME-MD. Anxiety and dysthymia modules	Common psychiatric comorbidity	Baseline
Brief Pain Inventory (BPI).	Pain severity and interference	Baseline, 3, 6 and 12 months
Hopkins Symptom Checklist (HSCL-20)	Severity of depressive symptoms, remission and response rates	Baseline, 3, 6 and 12 months
EuroQoL-5D	Health-related quality of life	Baseline, 3, 6 and 12 months
Sheehan Disability Inventory (SDS)	Disability due to psychological problems	Baseline, 3, 6 and 12 months
Form	Days of disability leave from work or interference with usual activities in the last month	3, 6 and 12 months
Patient Global Impression of Change (PGIC)	Patient’s perspective about the efficacy of treatment	3, 6 and 12 months
Use of health resources questionnaire	Number of primary care, specialist and emergency visits, and hospitalisations due to mental health or pain problems	3, 6 and 12 months
Satisfaction with care form	Patient’s satisfaction with clinical care received for depression and pain problems	3, 6 and 12 months
Exploration of the computerised database of pharmaceutical prescription and invoicing	Pharmacological treatments for pain and depression. Medical prescription and patient consumption	3, 6 and 12 months

#### Main outcome variables

In accordance with the aims of this study, the major outcome variables are the measurements of depression and pain severity as continuous variables, pain response rate, and depression response and remission rates.

The *severity of depressive symptoms* will be measured by means of the HSCL-20 (Hopkins Symptom Checklist, 20 items) [25]. The items are rated according to the presence of the symptom in the preceding two weeks on a Likert scale with five response options, from “not at all” (0 points) to “extremely” (4 points). The overall score, which can range between 0 and 4 points, is obtained by calculating the average of the 20 items.

*Clinical remission of depression* is defined as complete relief of symptoms and return to full functioning [26] An average point score less than or equal to 0.5 is an operational indicator of depression remission [27].

*Depression response to treatment* is a defined as a 50 % reduction in the severity of the symptoms with respect to the baseline HSCL-20 score [26].

The *pain intensity* and *pain interference* will be measured using the 15-item version of the Brief Pain Inventory [28, 29]. The BPI evaluates two dimensions: the intensity of the pain and its interference with everyday activities. The intensity of the pain is measured using multiple domains (worst pain experienced, minimum pain, average pain, and current pain), all of which are to be scored using a numerical rating scale from 0 (no pain) to 10 (worst pain). Interference with functioning is also measured using numerical rating scales from 0 (no interference) to 10 (total interference).

A *therapeutic response of pain* is considered relevant when a 30 % reduction is observed with respect to the baseline score [18].

*Health-related quality of life* will be measured with the EuroQol-5-D questionnaire [30, 31]. The EQ-5D has five scales (mobility, self-care, usual activities, pain/discomfort, and anxiety/depression) with three levels of severity (no problems, some problems, and extreme problems). A global score from 1 (the best state of health) and 0 (like being dead) can be obtained. The second part records the subject’s self-assessed health on a Visual Analogue Scale from 0 (the worst health status) to 100 (the best health status).

#### Secondary variables and effect modifiers

At baseline:Sociodemographic information: sex, age, marital status, education, labour status, and social class based on occupation [32].The severity of physical comorbidity will be measured using the Duke Severity of Illness Checklist (DUSOI) [33, 34]. For each diagnosis of a physical nature, a score is assigned to the symptoms, complications, prognosis and expected response to treatment. The overall severity of the patient is evaluated from 0 to 100.To assess the most common psychiatric comorbidity in depressed patients we will use the dysthymia and anxiety sections of the Primary Care Evaluation of Mental Disorders (PRIME-MD). This interview can generate a range of diagnoses of mental disorders according to DSM-IV criteria [35, 36].We will establish how long the current depressive episode has been evolving and any previous history of depression.

At the baseline and the follow-up interviews, we will also measure:The degree of disability caused by the psychological disorder will be evaluated using the Sheehan Disability Inventory (SDI) [37, 38]. This is a questionnaire with three items evaluating the disability in the areas of work, social life, and family. Two additional items evaluate the degree of stress and the perception of social support. The first four items are measured using visual analogue scales, from 0 (no effect) to 10 (extreme effect). Social support is evaluated in a scale from 0 % (non-existent social support) to 100 % (ideal social support).The patient’s perspective on the efficacy of treatment will be assessed using the self-report Patient Global Impression of Change (PGIC) [39]. This is a 7 point scale depicting a patient’s rating of overall improvement (from “very much improved” to “very much worse”).Patient satisfaction with the care will be evaluated using a single item: “How would you rate the quality of the care you have received (or how they have dealt with you) for your pain and/or depression problems?” with five response options in a Likert scale, from “excellent” to “bad” [40].Pharmacological treatments for pain and depression and use of health resources will be determined by means of interviewing the patient and exploring his/her computerised clinical records (i.e., prescription and pharmacy billing, number and type of primary care, specialist and emergency visits and hospitalisations for pain-related problems or depression-related problems).

### Statistical methods

#### Sample size

We will consider the response rates to treatment for depression and pain as reference variables. We will assume that the proportion of patients achieving a therapeutic response will be 50 % for both outcomes in the control group [14], and we expect a difference ≥17 % in the intervention group. Accepting an alpha risk of 0.05 and a beta risk of 0.2 in a two-tailed test, and with an expected loss of 15 %, 154 subjects are enough for each group. We will use the following formula to correct this figure for the design effect (randomisation by clusters): Deff = 1 + (m - 1) × ICC, where Deff: design effect; m: cluster size; and ICC: intraclass correlation coefficient [41]. Assuming an ICC of 0.01 [14] and m = 8, the Deff will be 1.07. As such, each study group will require 165 patients (1.07 × 154 = 165), distributed into 21 clusters of 8 patients each.

#### Analysis strategy

The randomisation will take place at the level of the primary care physicians (clusters), while the results of the intervention will be analysed at the individual-patient level [41]. The principal analyses will be by intention-to-treat, considering the patients from each group according to the initial assignment to the study groups, independently of compliance with the programme by either the individual patient or the physician.

We will compare the intervention group with the control group in order to verify that they are comparable in their baseline characteristics.

The main outcomes (dependent) variables are depressive symptoms (HSCL-20 score), response rate to the depression treatment, remission rate for depression, severity and interference of the pain (BPI), therapeutic response rate for the pain, and health-related quality of life at 3, 6, and 12 months.

In order to evaluate the effects of the intervention on the dichotomous variables we will use multilevel logistical regression models with mixed effects, adjusted by cluster, and employing an estimation of the Odds Ratio (95 % CI) of the intervention group with respect to the control group as a measurement of the effect. In order to measure the effect on the continuous variables we will use linear regression models with random effects (cluster), estimating the differences in adjusted averages (95 % CI) for the intervention group versus control group. For the main outcome variables we will calculate the intracluster correlation coefficient (ICC). Statistical significance will be established as *p <* 0.05. We will use STATA-12 and SPSS v.15 software for these calculations. This analysis strategy takes into account the design effect (randomisation by clusters) for any potential lack of independence among observations within the same primary care centre.

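### The analysis lists seven main outcomes at three visits under one p < 0.05 threshold, with no primary outcome, primary visit or success rule, and gives no priority to the two response rates that size the trial

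*Protocol article*

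**What the plan says.** Three sections of the protocol article bear on which result counts.

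- **Sample size.** "We will consider the response rates to treatment for depression and pain as reference variables". The error rates are set once: "Accepting an alpha risk of 0.05 and a beta risk of 0.2 in a two-tailed test". No visit is named, and nothing says whether one or both response rates must succeed.
- **Main outcome variables.** The opening sentence says that "the major outcome variables are the measurements of depression and pain severity as continuous variables, pain response rate, and depression response and remission rates". That is five outcomes, and the Abstract lists the same five. Pain interference and health-related quality of life are not in the sentence, but both are described further down under the same heading.
- **Analysis strategy.** "The main outcomes (dependent) variables are depressive symptoms (HSCL-20 score), response rate to the depression treatment, remission rate for depression, severity and interference", where the last two are the BPI scores. The list then closes with "therapeutic response rate for the pain, and health-related quality of life at 3, 6, and 12 months". Counting pain severity and interference separately, that is seven outcomes. The section adds "Statistical significance will be established as" p < 0.05, and makes no distinction among outcomes or visits.

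The Aim speaks of effectiveness over a 12-month monitoring period, which does not single out month 12.

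**The concern.** The trial is sized as if it had one test of a response rate at one time, but the analysis treats seven outcomes at three visits as equally main. Several different results could therefore become the headline, and the article gives no way to tell in advance which one answers the question. Two things are at stake. The 5% error rate quoted in the sample size does not describe the chance of a false claim from the whole set of main analyses. And if the main result is chosen after the arms have been compared, the choice may be driven by the data, which no later analysis can undo.

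Naming the primary outcome, its time point and the success criterion is protocol content. It defines the hypothesis and is not detail that is commonly left to a statistical analysis plan. The article does address the subject, with two lists of main outcomes and a threshold, but leaves it unsettled.

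**Working it through.** **1. The plan's own figure.** From Sample size: "the proportion of patients achieving a therapeutic response will be 50 % for both outcomes in the control group"; "we expect a difference ≥17 % in the intervention group", so 50% against 67%; two-sided alpha 0.05; power 80%; loss 15%; design effect 1 + (8 − 1) × 0.01 = 1.07.

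n = [1.96 √(2 × 0.585 × 0.415) + 0.842 √(0.5 × 0.5 + 0.67 × 0.33)]² / 0.17² = (1.366 + 0.578)² / 0.0289 ≈ 131 per group.

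With loss, 131 / 0.85 ≈ 154–155. The arcsine formula gives 130.4 / 0.85 = 153.5, that is 154. With the design effect, 154 × 1.07 = 165. The stated figures reproduce, for one comparison at one time. The planned 165 per group is worth 165 × 0.85 / 1.07 ≈ 131 independent evaluable patients.

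**2. Number of tests.** Table 1 schedules the HSCL-20, BPI and EuroQoL-5D at 3, 6 and 12 months. The models described have a random effect for cluster, and no joint test across visits is mentioned. One comparison per outcome per visit is therefore the natural reading:

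- 7 × 3 = 21 for the Analysis strategy list
- 5 × 3 = 15 for the opening sentence of Main outcome variables
- 2 × 3 = 6 for the sample-size variables

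**3. Chance of at least one p < 0.05 with no true effect.** If the k tests were independent, it is 1 − 0.95^k in either direction and 1 − 0.975^k in favour of the programme. They are not independent, and the article gives no correlations, so these are assumed: 0.3–0.6 between outcomes and 0.5–0.7 between visits. The correlated figures come from simulated normal test statistics, where the correlation of two statistics is the product of the outcome and visit correlations.

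| Tests | Independent: either / favourable | Correlated: either / favourable |
|---|---|---|
| 21 | 66% / 41% | 40–56% / 20–30% |
| 15 | 54% / 32% | 33–46% / 17–24% |
| 6 | 26% / 14% | 19–23% / 9–12% |

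Sensitivity for 21 tests: with correlations of 0.3–0.7 between outcomes and 0.4–0.7 between visits, the range is 35–58% in either direction and 18–32% favourable. With 0.6–0.8 within the depression and pain domains, 0.2–0.4 across domains and 0.5–0.7 between visits, it is 40–54% and 20–29%.

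**4. Power with two primary outcomes at one visit, planned size.** Power per outcome is 80% at alpha 0.05 and 71.2% at alpha 0.025.

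- Holm, both effects real, independent: 0.712 + (0.801 − 0.712) × 0.712 = 0.775 per outcome. It falls to about 76% at correlation 0.6. Power for at least one outcome is 1 − (1 − 0.712)² = 92% if independent and about 84% at correlation 0.6.
- Holm, only one effect real: 0.712 + 0.089 × 0.025 = 0.714, about 71%.
- Both required at p < 0.05: 0.80² = 64% if independent, about 67–70% at correlations 0.3–0.6.

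**The case against.** The strongest reply is that this is a condensed article with its analysis plan not shown, and that a multiplicity method is commonly left to such a plan. That stands as far as it goes: the absence of a named adjustment is not the finding. The finding is that the article states its main outcomes and threshold without saying which outcome, at which visit, decides the trial.

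Four stronger readings are tempting, and the document does not support them.

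- *The trial would be called positive by chance about half the time.* The 40–56% counts results in either direction, including those favouring usual care. The objective is better outcomes than usual care, and a false result in that direction has a chance of about 20–30% under the assumed correlations.
- *Any significant result satisfies the plan's rule.* The article gives a significance level and no success rule. Counting any one of 21 tests as success is an assumption made here to size the problem.
- *The 66% figure is realistic.* It is not. The HSCL-20 score, depression response and remission all come from one scale, and pain severity and pain response share BPI data.
- *Three sections give three rival lists of main outcomes.* The sample-size variables are inputs to a calculation, not a competing list. Pain interference and quality of life are described under the main-outcome heading. What remains is one opening sentence, echoed in the Abstract, that is shorter than the Analysis strategy list.

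It is also fair to object that 21 separate tests is an inference. The article does not say in so many words that each visit is tested on its own.

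**Conclusion.** The point holds. No primary outcome, primary visit or success rule is fixed, and the two response rates that justify 165 patients per group carry no priority in the analysis. The size depends on three assumptions: one test per outcome per visit, any significant result read as success, and the correlations stated above. Even the most charitable reading, with only the two sample-size variables tested at three visits, gives roughly four times the nominal 5% in either direction; its 9–12% in favour of the programme compares with a nominal 2.5%. The mismatch between the five-outcome sentence and the seven-outcome list is a minor inconsistency that should be tidied at the same time. This needs to be settled before any comparison by arm.

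**What to change.** Before outcomes are compared by arm, name depression response and pain response at one stated visit as the primary outcomes, with Holm across the two. Month 12, the end of the monitoring period, is one reasonable choice, but the sponsor should state which visit it wants. Make the remaining outcomes and visits secondary, and bring Main outcome variables, Sample size and Analysis strategy into agreement.

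The text cost is one paragraph in the protocol and analysis plan and a matching registry update, and some outcomes lose the label of main outcome. No new data are needed. The Trial Status section reports 130 of 330 patients recruited at 15 February 2016, with monitoring to December 2017, so at that date there was time to do this.

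There is a power cost, and it should be stated. With Holm at the planned size, power per outcome is about 76–78% if both effects are real and about 71% if only one is. If the sponsor instead requires both outcomes at p < 0.05, no alpha correction is needed, but joint power is about 64–70%, not 80%, and the sample-size section should say so. One primary outcome at one visit would keep 80% at the planned size. Splitting alpha to 0.025 each and restoring 80% per outcome would need 159 evaluable patients, 188 with loss and 188 × 1.07 ≈ 202 per group.

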### Random assignment to the study groups

To avoid potential contamination between the intervention and usual care, which could take place if the same physician were attending patients from the intervention group and the control group, the patients will be assigned to the study groups by clusters, with each cluster comprising patients belonging to the same physician’s roster.

The clusters from each primary care centre will be assigned to either the intervention group or control group by someone not otherwise involved in the study ([name], Spanish Society of Family and Community Medicine), following a simple randomised procedure using the List Randomiser tool at www.random.org. The physicians will commit to participate in the study prior to this assignment, and the patients will accept their recruitment without knowing which study group they will be assigned to.

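### The outcome models name cluster as the only adjustment; naming each continuous outcome's own baseline value as a covariate would add precision at no cost

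*Protocol article*

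**What the plan says.** The Analysis strategy section fixes a model for each type of outcome. Binary outcomes are analysed by "multilevel logistical regression models with mixed effects, adjusted by cluster", with an odds ratio as the effect measure. Continuous outcomes are analysed by "linear regression models with random effects (cluster), estimating the differences in adjusted averages". Cluster is the only term named in either sentence, and the second does not say what the averages are adjusted for.

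The section mentions baseline data once: "We will compare the intervention group with the control group in order to verify that they are comparable in their baseline characteristics". It attaches no consequence for the models to that comparison.

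Elsewhere in the article:

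- Table 1 schedules the BPI, HSCL-20 and EuroQoL-5D at baseline and at 3, 6 and 12 months.
- Under Main outcome variables, depression response is a "50 % reduction in the severity of the symptoms with respect to the baseline HSCL-20 score". Pain response counts "when a 30 % reduction is observed with respect to the baseline score". Remission is an absolute cut-off, a mean HSCL-20 score of 0.5 or less.
- Clusters are allocated "following a simple randomised procedure using the List Randomiser tool". No balancing on baseline severity is described.
- The Sample size section plans 165 patients per group in 21 clusters of 8, so 42 clusters in all.

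**The concern.** The baseline score on a scale usually predicts the follow-up score on the same scale. If it is left out of the model, the variation it explains stays in the residual and the confidence interval is wider than the data require. A chance difference in baseline severity between the arms also stays in the estimate, in proportion to how strongly baseline predicts follow-up. Comparing the arms at baseline shows such a difference but neither removes it nor recovers precision.

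What is at stake is the precision of the treatment differences on the HSCL-20, BPI severity and interference, and EQ-5D. All of these are listed among the main outcomes, and the data needed for the adjustment are already being collected.

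**Working it through.** **The plan's own figure.** Inputs from the Sample size section: 50% response in the control group, a 17-point difference (67%), two-sided alpha 0.05, power 80%, 15% loss, ICC 0.01, cluster size 8.

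- Evaluable patients per group: [1.96 × √(2 × 0.585 × 0.415) + 0.8416 × √(0.50 × 0.50 + 0.67 × 0.33)]² / 0.17² = 130.7, so 131.
- With 15% loss: 131 / 0.85 = 154.1; the plan has 154.
- Design effect: 1 + 7 × 0.01 = 1.07, and 154 × 1.07 = 164.8, so 165.

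The stated size reproduces. It rests on the two response rates and uses no baseline adjustment.

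**Precision on the continuous outcomes.** Effective patients per group: 165 × 0.85 / 1.07 = 131. In SD units, the standard error of the difference is √[2 × (1 − r²) / 131], and the difference detectable at 80% power is (1.96 + 0.8416) times that. The gain in equivalent patients is 1/(1 − r²) − 1. The article gives no r, so r is assumed; the design effect is held at 1.07 throughout.

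| Assumed r | Variance factor 1 − r² | Detectable difference (SD) | Equivalent unadjusted patients per group | Gain |
|---|---|---|---|---|
| 0 (no adjustment) | 1.00 | 0.346 | 165 | – |
| 0.3 | 0.91 | 0.330 | 181 | 10% |
| 0.5 | 0.75 | 0.300 | 220 | 33% |
| 0.7 | 0.51 | 0.247 | 324 | 96% |

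**Chance imbalance.** Assume the ICC of 0.01 also applies to the baseline scores.

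- SD of the baseline difference between arms: √(2 × 1.07 / 165) = 0.114 SD.
- 95% range: ± 1.96 × 0.114 = ± 0.22 SD.
- Without adjustment, a difference at that limit carries r × 0.223 into the outcome contrast: 0.07, 0.11 or 0.16 SD for r = 0.3, 0.5 or 0.7. Against the unadjusted detectable difference of 0.346 SD, this is 19%, 32% or 45%.

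These are values at the edge of the 95% range. At one SD of imbalance (0.114) the carry-over is 0.03, 0.06 or 0.08 SD.

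**The case against.** The strongest objection is that this is a condensed article. A covariate list is commonly left to a full protocol or analysis plan, and nothing in the text excludes baseline covariates. The averages are called adjusted in a sentence that names the cluster effect separately, so covariates may well be intended. This stands: the text is unspecified, and the loss of precision is conditional on the models being run as written. The request remains reasonable because the section does fix both models, and the only adjustment it states is cluster.

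A reader might infer more than the article supports:

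- *That the baseline comparison will select covariates.* The article says only that the arms are compared "in order to verify that they are comparable in their baseline characteristics". It describes no selection.
- *That the unadjusted result is biased, or the trial too small.* A randomised comparison without baseline covariates is unbiased on average, and its interval already allows for chance imbalance. No stated figure is wrong.
- *That imbalance passes in full into the effect.* It carries over only in proportion to r. Randomising by physician adds little: with a design effect of 1.07, the SD of the imbalance is about 3% larger (√1.07 = 1.034) than under individual randomisation.
- *That the same gain applies to every outcome.* The 1 − r² factor does not apply to odds ratios. Response and remission are binary, and the two response rates drive the sample size. Adding a prognostic covariate to a logistic model changes the odds ratio to one conditional on that covariate, and generally does not shrink the standard error of its logarithm. Response also already uses the baseline score in its definition.

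The size of the gain also depends wholly on r. Entry requires an average BPI pain score of at least 5 and a current major depressive episode. This narrows the baseline range and would tend to lower r, so the lower part of the table deserves weight.

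**Conclusion.** The point holds as an improvement to the continuous-outcome analyses, not as the correction of an error. Run as written, the analyses of the HSCL-20, BPI severity and interference, and EQ-5D would be valid but less precise than they could be. Under an assumed r of 0.3 to 0.7, adjustment would lower the variance to between 0.91 and 0.51 of its unadjusted value and the detectable difference from 0.346 SD to between 0.330 and 0.247 SD. The direction is the same for any r above zero; the size cannot be fixed from the article. The imbalance figures also assume a baseline ICC of 0.01. No numerical gain is claimed for response or remission, and 165 patients per group stands.

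**What to change.** State in the analysis plan that the mixed model for each continuous outcome includes the baseline value of the same scale as a covariate: HSCL-20 for depressive symptoms, BPI severity for pain severity, BPI interference for pain interference, and EQ-5D for quality of life. This also settles what the averages are adjusted for. State that the baseline comparison is descriptive and does not determine the covariates.

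For depression response, remission and pain response, baseline severity may also be pre-specified. If it is, say that the odds ratio is then conditional on baseline severity as well as on cluster.

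The cost is a sentence or two, with no new data and no change to the sample size. The article reports 130 of 330 patients recruited in February 2016 and follow-up until December 2017, so on its timetable the wording could be settled before the outcomes are analysed.
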